#### Neurophysiology

Substrates of response: transcranial magnetic stimulation (TMS) noninvasively measures cortical and corticospinal neurophysiology
[59]. In the present pilot trial, TMS defines efficiency of conduction via residual corticospinal tracts
[56], the structural integrity of which is outlined with diffusion tensor imaging. TMS also measures conduction between both hemispheres relayed via transcallosal pathways; this conduction is normally inhibitory, that is, one hemisphere exerts inhibition upon another, and that in return exerts counter-inhibition. In stroke, balance of such inhibition is disrupted. Whereas inhibition from the intact stroke-affected hemisphere is exaggerated, that in the opposite direction is diminished
[60]. We explore whether tDCS delivered to PMC in the stroke-affected hemisphere improves the efficiency of corticospinal conduction and helps rebalance inhibition exerted between the intact and stroke-affected hemispheres.

### Randomization

We are using randomization blocks in sizes of four, where two patients in a block are assigned to PMC tDCS plus CIMT and the other two to the sham tDCS plus CIMT group. Such block randomization prevents the possibility that several patients in a row would get randomized to tDCS or sham tDCS groups in the early part of the study. The order of patients in blocks is random, generated using an online tool. Allocations are concealed in an opaque envelope and hidden in a locked cabinet with restricted access; they are opened by an investigator not involved in data collection or analysis before the first day of treatment.

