## Methods

### Study design

We use a pilot, randomized, sham-controlled, double-blind clinical study design. Twenty patients are being randomly assigned to PMC tDCS plus CIMT or sham tDCS plus CIMT groups. All outcomes are collected at pretest and at post-test after 5 weeks of intervention. At 3-month follow up, outcomes of hand function are collected to examine retention.

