### Recruitment

This is a single-center pilot clinical study. Patients with chronic stroke are being recruited from nine area hospitals within the Cleveland Clinic health system through outpatient and community-based stroke programs, referrals from providers, medical chart review, liaison with local support groups, and spontaneous demand through newspaper, radio and website advertisements.

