### Initial screening

Patients are initially screened by telephone, followed by thorough chart review. The physical therapist, principal investigator and study coordinator evaluate subjects, who provide written informed consent in person, to ensure eligibility. Diagnosis and eligibility are confirmed at screening by a neurologist. Screening for neuroimaging and brain stimulation is repeated at each of these levels.

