### Interventions

#### CIMT

Once patients are randomly assigned to respective groups, patient-specific rehabilitation is delivered under supervision of the study principal investigator and physical therapist (EP) in an outpatient setting at the Cleveland Clinic main campus. All patients receive CIMT for 30 minutes, twice a day, 3 days a week for 5 weeks. It includes massed (intensive) functional exercises for the paretic upper limb guided by the principle of shaping
[47], which involves a graded, regimented, feedback-driven approach to achieving impairment- and patient-specific goals. Tasks focus upon transfer to real-world activities, including activities like grooming, making a telephone call, et cetera. The protocol of CIMT discussed here differs slightly from the modified version of the program that is generally employed
[46]. Instead of one 30-minute session, we deliver two 30-minute sessions; rather than 10 weeks, we deliver CIMT for 5 weeks, at the same frequency, that is, three times a week. We have incorporated this frequency and length to improve compliance, as patients are required to visit the outpatient clinic 15 times over 5 weeks rather than 30 times over 10 weeks. Patients’ use of the non-paretic upper limb is restrained by placing it in a mitt, which they are asked to maintain for 2 hrs every weekday during peak times of activity, instead of 5 hrs.

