### Trial status

The trial is actively enrolling.

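### A single published block size of four at one enrolling centre makes about a third of assignments certain to any screener who knows the earlier arms: a minor, conditional risk that is cheap to reduce

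*Protocol article*

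**What the plan says.** All references are to the protocol article.

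- **Randomization** fixes one block size and its split: "We are using randomization blocks in sizes of four, where two patients in a block are assigned to PMC tDCS plus CIMT". Sham is given to the remaining pair, so the split is 2:2. On order it says "The order of patients in blocks is random, generated using an online tool". Allocations are kept in opaque envelopes in a locked cabinet with restricted access. An investigator with no part in data collection or analysis opens them before treatment starts.
- **Study design**: "Twenty patients are being randomly assigned to PMC tDCS plus CIMT or sham tDCS plus CIMT groups". **Recruitment**: "This is a single-center pilot clinical study". No stratification is described, so the list is one sequence of 20/4 = 5 complete blocks.
- **Initial screening**: "The physical therapist, principal investigator and study coordinator evaluate subjects, who provide written informed consent in person, to ensure eligibility". A neurologist then confirms diagnosis and eligibility.
- **CIMT** (under Interventions): "patient-specific rehabilitation is delivered under supervision of the study principal investigator and physical therapist".
- **Blinding** names patients and outcome assessors as blinded. It does not mention those who supervise treatment.
- **Trial status**: "The trial is actively enrolling".

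**The concern.** Envelopes and a locked cabinet stop someone from reading the next allocation. They do not stop someone from deducing it when the block size is known and the earlier arms in the block are known. Here the size is known to the team and has been published during recruitment, and two of the roles that judge eligibility also supervise treatment.

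At stake is selection bias. A screener who can foresee the next arm could, even without intending to, delay, bring forward or decline a patient. The article itself expects response to depend on who is enrolled. With 10 patients per arm, replacing one non-responder by a responder moves that arm's responder proportion by 1/10, or 10 percentage points.

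**Working it through.** The article gives no predictability figure, so there is none to reproduce. Inputs: block size 4, split 2:2, random order (Randomization); 20 patients (Study design); one centre (Recruitment).

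**1. Certain assignments when earlier arms are known.** A 2:2 block has 6 equally likely sequences. In 2 of them (AABB, BBAA) the third and fourth assignments are certain. In the other 4, only the fourth is.

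- Expected per block: (2×2 + 4×1)/6 = 8/6 = 1.333, and 1.333/4 = 33.3%.
- Over 5 blocks: 5 × 1.333 = 6.67 of 20.
- Minimum 5×1 = 5 (25%); maximum 5×2 = 10 (50%).
- The number of blocks with two certain positions is Binomial(5, 1/3). The probabilities of 5, 6, 7, 8, 9 and 10 certain assignments are 0.132, 0.329, 0.329, 0.165, 0.041 and 0.004.

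**2. Best guess when earlier arms are known.** By position, the chance of a correct guess is 1/2, 2/3, 2/3 and 1. The mean is 2.833/4 = 70.8%, or 14.17 of 20, against 10 of 20 by chance.

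**3. Earlier arms only guessed.** Let each earlier arm be guessed independently with accuracy q, and let the next arm be predicted optimally from those guesses. No assignment is then certain.

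| q | correct predictions |
|---|---|
| 0.5 | 50.0% |
| 0.6 | 53.0% |
| 0.7 | 56.2% |
| 0.8 | 60.1% |
| 0.9 | 64.9% |
| 1.0 | 70.8% |

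**4. How far partial knowledge reaches.** One known patient identifies nobody: each other patient in the block has the opposite arm with probability 2/3. Two known patients identify the other two only if both are in the same arm, which has probability 1/3. Otherwise three must be known.

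**5. Effect of mixed sizes.** The size sets are assumptions. The simulation (3,000 lists) covers 20 patients; the guesser knows the possible sizes and all earlier arms, but not the order of sizes.

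| sizes | certain | best guess correct |
|---|---|---|
| 4 only | 33% | 71% |
| 2, 4 | 11% | 72% |
| 4, 6 | 6% | 69% |
| 2, 4, 6 | 4% | 70% |

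These lists draw sizes freely and are cut off at 20. A list built to end exactly at a total the guesser knows gives some certainty back, since the last assignment at least (1/20 = 5%) is always deducible. I repeated the simulation with every order of sizes summing to 20 equally likely and the total known (20,000 lists). It gave about 13% certain for 4 and 6, and about 8% for 2, 4 and 6, with best guesses at about 70% and 72%. Either way most of the certainty goes and little of the guessing advantage does.

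**The case against.** The strongest reply is that no text says anyone who screens ever learns an arm. The treating supervisors are not listed as blinded, but silence in a condensed article does not make them unblinded, and who operates the stimulator is a detail that a full protocol may settle. The tDCS section gives sham patients the same 1 mA onset and ramps the current slowly in everyone, so tingling is a weak clue. Access to the envelopes is restricted, a neurologist confirms eligibility, and the main thresholds (more than 6 months since stroke, at least 10° of extension) are measurable. This is also a small pilot that calls itself exploratory. All of that stands, and it sets the severity.

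A reader might infer that a third of assignments can be worked out from guessed arms, or that identifying one or two patients unmasks the rest of the block. Steps 3 and 4 show that neither follows. A reader might also infer that treatment staff are unblinded or that selection has been biased. The article supports neither.

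What the reply does not remove is the structural point. The safeguards act on reading the envelope and on entering ineligible patients. They do not act on deducing the next arm, or on the timing and order of eligible patients. The envelope opener is kept out of data collection and analysis, but the text does not say that this person is outside screening or treatment.

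**Conclusion.** The point holds as a minor, conditional risk of selection bias. The one-third figure is an expectation, and it rests on one assumption that the article neither states nor excludes: that a person who screens correctly knows the earlier arms in the current block. Under good but imperfect guessing the advantage is modest, and at chance accuracy it is zero. Nothing in the Randomization section is miscalculated or contradictory. The case for a change is that a single disclosed block size creates avoidable certainty, and that most of it can be removed at almost no cost.

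**What to change.** For the allocations still to be made, have someone outside screening, treatment and assessment regenerate the unused envelopes in a random order of mixed block sizes, for example 4 and 6, or 2, 4 and 6. The sizes should sum to the remaining patients. Start after the current block is complete, so that the total still ends at 10 per arm. Withhold the sizes from everyone who screens, treats or assesses, and describe them in the protocol only as varying and undisclosed. Also state whether those who screen and supervise treatment are kept unaware of the arm, since the whole risk turns on that.

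The cost is a new set of envelopes and a temporary imbalance of up to 3 within a block of six, against 2 within a block of four. That imbalance may persist if enrolment stops early. The benefit depends on how many patients remain, which the article does not give. With 8 left, for instance, sizes 4 and 6 can only be 4 + 4, which changes nothing, so the set 2, 4 and 6 is the more useful late in enrolment.

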#### Structural neuroimaging

Predictors of response: diffusion tensor imaging defines the structural patency of white matter tracts
[55]. Using this method, we evaluate the integrity of corticospinal tracts, which are considered most critical to dexterity
[56]. We anticipate that PMC-based tracts will be more predictive of recovery with tDCS than those emerging from M1.

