### Sample size estimation

The sample size has been estimated based on previous studies that have paired invasive or noninvasive stimulation with rehabilitation
[8,9,12,17,31]. Because UEFM has been most commonly investigated across the majority of studies, we used the effect sizes calculated across these studies to generate several permutations of sample size and the corresponding extent of change in the UEFM score (Figure 
2) to estimate power. Using a method of simulations
[63] where 500 simulations were performed, we estimated sample sizes that would generate significant differences upon the UEFM based on a mixed-effects model. From this method, we have found that a sample size of 10 per group would yield 83% power (95% CI 79.41 to 86.19%) to detect differences between groups (PMC tDCS plus CIMT sham tDCS plus CIMT group), 99.6% power to note differences across time (95% CI 98.56 to 99.95%) and 97% power (95% CI 95.35 to 99.46%) to observe a group X time interaction (Figure 
2).

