**Figure 2 F2:**
[figure not shown]
**Power analysis: power was determined by simulation.** Lower and upper lines define exactly the 95% CI for power, calculated based on the binomial distribution. N is the total sample size. The analysis was performed at a 0.05 significance level considering 2 × 2 factorial analysis of variance (ANOVA) (tDCS plus CIMT and sham tDCS plus CIMT from pretest to post-test). Power has been estimated here for an interaction term (A *C).

Although the estimated sample size appears small, it is commensurate with the pilot exploratory nature of our study. Pilot studies involving brain stimulation generally use smaller sample sizes compared to rehabilitation trials
[28] because contraindications to brain stimulation/imaging are constraining. Still, we anticipate having adequate statistical power based on prior evidence where despite enrolling a total of 14 to 30 subjects, several studies report significant benefit of adjunctive stimulation
[8,30,44]. Additionally, use of a repeated-measures design further provides greater power. Studying neural mechanisms with fMRI and tractography in limited sample sizes is challenging. Given the exploratory nature of our pilot study, we would be able to highlight elemental neural mechanisms of recovery. Previously, in a three-group, randomized controlled study design with a small sample of 20, we deciphered correlates of fMRI
[37]. Recently too, Stagg *et al*.
[64] show differences in fMRI activation across varying types of tDCS interventions in 11 patients with stroke. Without overemphasizing the importance of small pilot studies, we stress instead the significance of large-scale studies in generating clear evidence of efficacy. Our current pilot exploratory study is a step in that direction as it would offer estimates of effect size related to PMC tDCS and neural markers that can serve as entry criteria.

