### Statistical and data analyses

Feasibility: analysis of feasibility includes investigating the rigor of experimental blinding and determining compliance with the 5-week outpatient rehabilitation program. A chi-square analysis will determine whether patients in one group versus another estimate their group assignment correctly. Investigators also complete a similar questionnaire at the end of the study. While patient responses will indicate the rigor of the blinding procedures, responses from investigators will ensure investigator equipoise, preventing observer bias. Attrition or missing data will be analyzed using a strategy known as multiple imputations
[65], where each missing value is replaced with a set of plausible values that represent the uncertainty about the true value. The multiple imputed data sets are analyzed using standard procedures used for complete datasets and by combining results from these analyses. The method of multiple imputations does not attempt to estimate each missing value through simulated values, but rather represents a random sample of missing values. This process results in valid statistical inferences that properly reflect the uncertainty due to missing values.

Safety: the incidence of adverse events in each group will be computed as a proportion of individuals in each group who experienced side effects. We will be using the Fisher exact test to contrast the incidence of side effects between both groups.

Efficacy and markers of recovery: our primary endpoint of efficacy is the UEFM. Secondary outcomes include nine-hole peg test, Action Research arm test, motor activity log, finger abduction strength and the modified Ashworth scale of spasticity. A general linear mixed-model approach will be followed to analyze functional outcomes across three levels of time (pre, post, and follow-up). Significant two-way interaction, whenever present, will be explored using the Tukey honestly significant difference (HSD) test. Non-parametric tests will be used if the distribution is not normal.

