## Discussion

We have described the protocol of our ongoing pilot clinical study in chronic stroke, where we test safety, feasibility, efficacy and neural markers of upper limb rehabilitation combined with stimulation targeting the PMC in the affected hemisphere. Evidence on the value of paired cortical stimulation in rehabilitation is divided due to theoretical and design-related issues. Stimulating peri-lesional and affected M1 without knowing the individual substrates of recovery creates variability in response
[4,19,67]. Differences in design, such as type of control, blinding and safety-feasibility trade off of varying types of stimulation have further added confusion to evidence of efficacy. Recent trials have also failed at the phase III level due to poor estimation of the magnitude of the placebo effect
[19,68]. Therefore, to prepare for future trials, we propose targeting the PMC in the affected hemisphere with the rationale that it may serve as an alternative locus of recovery. We employ tDCS, which may be safer and feasible to apply online during long-term outpatient rehabilitation; based on its ability to provide a more effective placebo, it permits us to adopt double blinding and sham control, helping estimate the magnitude of placebo. Finally, we identify patient-specific indicators of recovery to stratify responders for design of future investigations.

Knowing markers of response versus non-response to brain stimulation in rehabilitation would not only harmonize evidence in the field, but will also help us select candidates for subsequent trials. Early clinical trials of invasive stimulation showed greater promise of adjuvant stimulation
[8-10] than recent phase III
[15,19], potentially since patients in earlier trials possessed functioning corticospinal pathways
[9] unlike only a few in phase III
[19]. Similarly, rehabilitative outcomes are invariably successful for well-recovered patients
[14,22], unlike for those with moderate/severe paresis
[16,18,31]. Subcortical lesions respond better
[13,29] than massive infarcts of total anterior circulation

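### With 10 patients per arm, the stated UEFM comparison adjusts neither for corticospinal tract integrity nor for the link between baseline UEFM and gain; this can cost precision and clarity, though not validity

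*Protocol article*

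**What the plan says.** **Allocation.** The Randomization section states: "We are using randomization blocks in sizes of four, where two patients in a block are assigned to PMC tDCS plus CIMT". The other two patients in each block go to sham. The only purpose given is to avoid runs of one arm, and no patient characteristic is balanced.

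**Efficacy model.** Under Statistical and data analyses: "A general linear mixed-model approach will be followed to analyze functional outcomes across three levels of time (pre, post, and follow-up". Significant two-way interactions are to be explored with Tukey's test. No covariate is named.

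**Tract integrity.** The Structural neuroimaging section says "we evaluate the integrity of corticospinal tracts, which are considered most critical to dexterity". The Discussion explains why early invasive-stimulation trials did better than phase III in these terms: "potentially since patients in earlier trials possessed functioning corticospinal pathways". It also contrasts good outcomes in well-recovered patients with poorer ones in moderate or severe paresis.

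**Where these factors are used.** Baseline UEFM and tract function and integrity are listed for the t-test comparison of responders with nonresponders. The same section considers modelling predictors of UEFM change and declines for lack of power. Tract integrity appears in no stated comparison of tDCS with sham.

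**The concern.** The protocol offers corticospinal integrity and severity as reasons why earlier trials disagreed, and it measures both at pretest. The stated arm comparison then leaves tract integrity out altogether, and uses baseline UEFM only as the starting level of the outcome. In a trial of 20, chance differences in such factors are common.

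At stake is how well the one effect estimate can be read. The Sample size estimation section says the pilot is meant to supply effect-size estimates for PMC tDCS and markers for use as entry criteria. If the arms differ visibly on tract integrity and no adjusted analysis was prespecified, readers cannot tell how much of the observed difference goes with that imbalance. Adjustment chosen after the data are seen would be less convincing.

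**Working it through.** **1. The plan's own figures.** The inputs are "a sample size of 10 per group would yield 83% power (95% CI 79.41 to 86.19%) to detect differences between groups", "97% power (95% CI 95.35 to 99.46%) to observe a group X time interaction" and "where 500 simulations were performed", with Figure 2 adding: "The analysis was performed at a 0.05 significance level considering 2 × 2 factorial analysis of variance (ANOVA". The text gives no effect size, SD or pre-post correlation, so the power values cannot be rebuilt. Exact binomial intervals can be checked:
- 415/500 gives 79.41 to 86.19%, as printed.
- 498/500 gives 98.56 to 99.95%, as printed.
- 486/500 gives 95.35 to 98.46%. The printed upper limit of 99.46% does not fit. This is a separate small correction.

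Under a two-sample t test with 10 per arm, 83% power corresponds to a difference of about 1.38 SD and 97% to about 1.82 SD.

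**2. Chance imbalance, continuous factor.** The SE of a standardised baseline difference is √(1/10 + 1/10) = 0.447 SD.
- P(difference above 0.5 SD) = 2[1 − Φ(0.5/0.447)] = 26%.
- For at least one of two independent factors: 1 − (1 − 0.264)² = 46%.
- P(above 1 SD) = 2.5%.

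**3. Chance imbalance, binary factor present in 10 of 20.** P(7:3 or worse) = 2(120² + 45² + 10² + 1²)/184,756 = 33,052/184,756 = 17.9%. Simulating five blocks of four also gives 17.9%, so blocking on numbers does not reduce it.

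**4. Effect on the estimate.** The shift is correlation × imbalance. At 0.5 SD and assumed correlations of 0.3, 0.5 and 0.7 it is 0.15, 0.25 and 0.35 SD.

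**5. Baseline UEFM.** With equal pre and post SDs and pre-post correlation r, a change comparison carries over −(1 − r) of a baseline imbalance: −0.5, −0.3 and −0.1 at r = 0.5, 0.7 and 0.9. ANCOVA carries over about 0. Simulated SEs at those values of r are 0.445, 0.348 and 0.199 SD for change, and 0.399, 0.328 and 0.197 SD for ANCOVA.

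**6. What adjustment gains or costs.** With n = 20 and q covariates, the variance ratio (adjusted to unadjusted) is (1 − R²)(n − 3)/(n − q − 3).
- One covariate, R² = 0: 17/16, or the precision of 20 × 16/17 = 18.8 patients, a loss of about 6%. Simulated equivalents at correlations 0.3, 0.5 and 0.6 are 20.6, 25.2 and 29.3 patients.
- Two covariates: 17/15 at R² = 0. Break-even is R² = 2/17 = 0.12.

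Simulation with two covariates and a true difference of 1.40 SD (unadjusted power about 84%):

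| Joint R² (assumed) | Adjusted power | Adjusted SE (SD) |
|---|---|---|
| 0 | 79% | 0.47–0.48 |
| 0.10 | 83% | 0.45 |
| 0.25 | 89% | 0.41–0.42 |
| 0.50 | 97% | 0.33–0.34 |

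The unadjusted SE is about 0.45 SD throughout. Type I error was 4.6 to 5.3% with or without adjustment.

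**7. Form of the covariate.** If tract integrity X enters only as a main effect γX, then for a patient with both visits post − pre contains γX − γX = 0. The group-by-time contrast is therefore not adjusted.

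**The case against.** Several stronger readings are tempting, and the document does not support them.

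- **That severity is ignored.** It is not. Pretest UEFM is an outcome level in the model and the responder rule is a gain, so much of a baseline difference is removed. What remains is the link between baseline and the amount of gain.
- **That the protocol treats tract integrity as settling who improves.** Its wording is conditional throughout, and testing the marker is an objective of the trial. Calling the tracts critical to dexterity is a statement about hand function, not about gain. Enrolment of mild-to-moderate impairment also narrows the severity contrast.
- **That imbalance biases the result or produces false positives.** Randomisation already accounts for it, and type I error is unaffected. As an illustration with invented responder rates of 80% (good tracts) and 30% (poor tracts), a 7:3 split gives 0.7 × 0.8 + 0.3 × 0.3 = 0.65 against 0.3 × 0.8 + 0.7 × 0.3 = 0.45. That is 6.5 against 4.5 responders out of 10, with p about 0.37.
- **That the allocation method should be changed.** Moving to minimisation during enrolment of a 20-patient pilot would require imaging processed before each allocation and a high/low cut that the protocol does not define. Measurement before allocation is itself implied by the order of procedures, not stated. Simple blocking is defensible here.

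Two further objections carry weight. An unseen analysis plan may name covariates, so the point concerns the analysis as stated. However, the article does discuss modelling predictors of UEFM change and declines, which makes silence harder to read as deferral. Second, the document gives no correlation between these factors and UEFM gain, so the benefit of adjusting is uncertain.

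**Conclusion.** The point holds in a limited form. As stated, the arm comparison of UEFM does not adjust for tract integrity or for the dependence of gain on baseline UEFM. A baseline difference above 0.5 SD in any one such factor is expected in about 26% of randomisations of this size. The validity of the test is intact. The consequences are possible loss of precision and an effect estimate that is harder to interpret.

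The imbalance probabilities follow from 10 per arm and need no clinical assumption beyond approximate normality or, for the split, 50% prevalence. The size of the shift and the gain from adjusting rest on assumed correlations. This is a worthwhile prespecification for a trial that is still enrolling, and not an error that undermines it.

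**What to change.** In Statistical and data analyses, prespecify that the arm comparison of UEFM change is adjusted for baseline UEFM and for one pretest measure of stroke-side corticospinal tract integrity, named before unblinding. Either of two forms works:

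- ANCOVA on the post-test score with both covariates.
- A mixed model with covariate-by-time terms. If baseline UEFM is a covariate there, it should not also remain an outcome level, so post-test and follow-up become the outcomes.

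A main effect added to the present three-level model is not enough, because it leaves the group-by-time test unadjusted. Report the unadjusted result alongside. Leave the allocation scheme as it is.

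The cost is analysis-plan wording and about one degree of freedom per covariate, with no extra patients, visits or procedures. The downside is a small loss of precision if the covariates do not predict gain: about 6% for one covariate, or power of about 79% in place of 84% for two. Two covariates pay only above a joint R² of about 0.1.
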